## Abstract

**Background:**

Families with minor children affected by parental cancer are at risk of considerable emotional and organizational stress that can severely burden all family members. So far, there has been a lack of comprehensive support services for affected families. The aim of this project is to implement and evaluate a complex psychosocial intervention for these families by providing advice, information, and care on an emotional, psycho-social, and communicative level during and after the cancer experience and across healthcare sectors.

**Methods:**

Family-SCOUT is a project supported by the German Innovation Fund (https://innovationsfonds.g-ba.de/). The evaluation is based on a mixed-methods quasi-experimental design with the intervention and control groups. A standardized postal survey at three measurement points (T0: study enrollment; T1: 3 months of follow-up; T2: 9 months of follow-up), secondary data from the participating health insurance funds, and semi-structured qualitative interviews are used for summative and formative evaluation. The study aim is to include *n*=560 families. Data will be analyzed according to the intention-to-treat principle. The primary analysis is the comparison of the Hospital Anxiety and Depression Scale (HADS) response rates (minimal important difference (MID) ≥ 1.6 in at least one of the two parents) at T2 between the intervention and control group using Fisher’s exact test. The conduct of the study as well as the development and implementation of the intervention will be accompanied by comprehensive study monitoring following the principles of an effectiveness-implementation hybrid study.

**Discussion:**

The results will allow to test the effectiveness and efficiency of the intervention for the target group. The first experience with the implementation of the intervention in model regions will be available. The evaluation results will serve as the basis to assess the need of including the intervention in the catalog of services of the statutory health insurance funds in Germany.

**Trial registration:**

ClinicalTrials.gov, NCT04186923. Retrospectively registered on 4 December 2019.

**Supplementary Information:**

The online version contains supplementary material available at 10.1186/s13063-021-05577-y.

## Background

Each year, approximately 100,000 children (50,000–150,000) in Germany experience that one of their parents develops cancer (expert estimate, Robert Koch Institute, 2017). In a representative survey in the USA, 14% of cancer patients had underage children [1]. The sudden interruption of familiar everyday routines and the noticeable sense of uncertainty are expected to double the risk for the development of psychological symptoms (anxiety, depression, and psychosomatic complaints) in children confronted with parental cancer compared to children in the general population [2]. These symptoms tend to be rare at the time of diagnosis and often develop during the course of the parent’s cancer treatment or follow-up [3]. In addition, unaffected parents providing support also show remarkably high-stress levels [4] along with a significantly increased risk of morbidity [5]. In a Danish study, a significant increase in in-patient hospital stays due to affective disorders in partners of breast cancer patients was demonstrated over a 13-year follow-up period [6].

To date, the standard support provided in Germany covers domestic help for a maximum of 26 weeks, when children under the age of 12 live in the household. However, the sick leave times of severely ill parents are often much longer. Furthermore, as this type of support is directly linked to the patients’ health insurance status, this sole orientation towards the parent suffering from cancer himself results in the paradox that, at the moment of the patients’ death, support will end immediately, which is the exactly the point in time when remaining family members are at the highest need for support. Consequently, the burden on the other family members and their increased risk for the development of subsequent and potential long-term sequelae and even more so, the initiation of preventive measures thereof are not adequately addressed. Although numerous studies have defined stress factors, risk patterns, and effective interventions for families with a severely ill parent [7], they are neither integrated into standard care nor into prevention plans in Germany. The problem can be further accelerated by the fact that support offered by cancer counseling centers is rarely used by the often-overburdened families, while special services for children are only provided within selected cancer counseling centers [8]. Along this line, hospitals’ social service staff is often not adequately equipped for complex interventions, and potentially helpful interventions offered during or close to the time of initial diagnoses are often neglected [2]. Additionally, access to support by social workers outside of hospital care is hard to find leading a substantial “cross-sectional” gap in the availability of psychosocial care. This phenomenon is somewhat further complicated by the current shift towards more outpatient systemic cancer treatments.

The limited links between the different sectors and the complexity of different service providers involved ultimately lead to structurally insufficient care for the families. Parents are often under severe emotional and organizational stress and therefore often fail to organize the support needed for themselves. Consequently, during the subsequent course of the disease, they may acquire increased morbidity and mortality risks [6, 7]. Risk factors for increased psychological impairment are dysfunctionality in the family and the psychological burden on the parents. In particular, the ease up on psychological burdens for parents, the availability of possible coping strategies, functioning family structures, protective relationships, and open communication within the families are more decisive for the later outcome for all surviving members of the family than medical factors such as prognosis and severity of the disease [9, 10]. This is the starting point for the cross-sectional, multi-professional initiative “family-SCOUT”.

### Description of the intervention

#### Intervention: Family-SCOUT

In order to describe family-SCOUT, we used the TIDieR-checklist [11] for complex psychosocial interventions. The main goal of family-SCOUT is to provide support for families with minors suffering from parental cancer. Both parents (or a single affected parent) should have the chance to reduce stress levels while the overwhelming burden and parentification of their children should be avoided. Parents’ capabilities to emotionally support their children in coping with the new situation should be strengthened. Furthermore, resources allowing the parents themselves to establish the adaptations of their daily life required should be provided. Mental disorders particularly also in the later life of all family members should be prevented.

#### Active outreach support

Patients with an oncological disease and underage children will be identified by physicians, psycho-oncologists, or social workers working in the field of medical, i.e., oncological care. If consented by the affected patient, a member of the family-SCOUT-staff will be contacted. Subsequently, families will be offered an initial counseling session either within the hospital, at the outpatient clinic of practice, or at the families’ home in order to allow organizationally and emotionally overburdened families to make use of available support structures and interventions.

#### Permanent contact person/family-SCOUT

The family-SCOUT provides a continuous contact throughout the entire course of disease including palliative situations, dying, death, and bereavement depending on the family’s need. Professionals working as family-SCOUTs have different backgrounds such as social workers or nurses with additional qualifications in psychotherapy. Additional training involves communicative skills, training in psycho-oncology, developmental psychology, and social law (80 h). The main tasks of the family-SCOUTs are related to all topics covering the family’s concerns, e.g., difficulties in organizing child care, needs for household support, self-assessment of communication behavior in the family, and ways of coping. The family-SCOUTs provide information about all options available for organizational, emotional, and communicative purposes and facilitate access to existing support services, e.g., domestic help, youth welfare services, cancer counseling services, and psycho-oncological services either face-to-face or by telephone. The family-SCOUTs also foster open discussions about the disease between parents and subsequently all family members and provide appropriate brochures and recommendations for reading materials designed for children.

Periods of intervention depend on the affected family’s needs; the observation time within the study is at least 9 months. In palliative situations and in the case of death, companionship by the family-SCOUT continues until stable everyday structures have become re-established and necessary support (e.g., psychotherapeutic support) can be securely offered within a stable framework. If single parents with an unfavorable prognosis are in need, support is provided for arranging a custody declaration in the case of death.

Through the outreach program of the Center for Integrated Oncology (CIO) Aachen-Bonn-Cologne-Duesseldorf (CIO^ABCD^), the family-SCOUT initiative will be closely connected regionally with oncologists in the inpatient and outpatient sectors, social services in the local hospitals, psycho-oncologists, youth welfare staff, pediatric psychotherapists, pediatric psychiatrists, and medical/psychological psychotherapists with training in family therapy.

#### Specific family-centered and child-centered therapeutic interventions

When reaching their limits in open discussions with the families, the family-SCOUTs may involve specially trained therapists working on the basis of the COSIP (Children of Somatically Ill Parents) manual [12]. They will reinforce the parents’ skills, promote open discussion within the family, and support the children in coping with the given scenario by taking development-psychological aspects into account in an age-appropriate fashion. The setting may involve parental sessions, family sessions, and children sessions. No prior ICD diagnosis is required to receive the sessions fostering the preventive approach of the family-SCOUT concept.

#### Family-independent tasks of the family SCOUT

In order to provide support, the family-SCOUTs engage in networking with the staff of medical or social sectors and managing interfaces between the in-patient and outpatient sectors, psycho-oncologists, pediatric psychotherapists, pediatric psychiatrists, and between families and public services (school, kindergarten) as well as the healthcare system and the youth welfare system.

## Methods/design

### Trial design

Through a pilot project in Aachen, this new form of care described here has already completed the phases of theory formation, modeling, and exploratory testing, including phase II in accordance with Campbell et al. [13] and feasibility testing or piloting in accordance with MRC (Medical Research Council) [14] under the name “Brückenschlag.” Within the follow-up project family-SCOUT, interventional levels described are now to be modeled in an appropriately complex evaluation design in order to test the benefits and appropriateness [15] and the degree of success of the intervention’s implementation. This study design combines elements of clinical effectiveness and implementation research in an effectiveness-implementation hybrid study type 2 [16]. The family-SCOUT effectiveness evaluation is based on a quasi-experimental, non-randomized control group design with two study arms (an intervention group (IG) and a control group (CG)), as well as one time point for preliminary measurement and two time points for follow-up measurements.

### Participants

The study participants will be recruited consecutively in four regions over the recruitment period. Since the support structure in Aachen already existed due to the pilot project, it was ethically not reasonable to withhold the existing service from the patients there; thus, the other regions serve as the control group. In order to be able to depict the implementation of the intervention in another region, the allocation in Bonn was changed during the project. The control group was recruited in the first project phase (during the development of the intervention infrastructure) and the intervention group in the second phase (when the new supporting structures were available). Accordingly, participants in the control group had the option to switch to the intervention group later. In Aachen, the families will be recruited through the Center for Integrated Oncology (CIO) Aachen (CIO^A^, region 1). In Bonn, the families will be recruited through the CIO^B^ and through the Bonn Tumor Center (region 2). In Düsseldorf, the families will be recruited through CIO^D^, region 3) (Fig. 1). In addition, families will be recruited for semi-structured interviews in the Bad Oeynhausen region through the Specialist Clinic for Oncological Rehabilitation and Follow-up Rehabilitation in Bad Oexen (region 4).

**Fig. 1 Fig1:**
[figure not shown]
Flowchart of participant flow through the trial and allocation of the intervention to the recruitment sites. SHI statutory health insurance, FPI first patient in, LPI last patient in, LPO last patient out

#### Inclusion criteria

Confirmed ICD diagnosis of cancer in one parent

Custody of at least one underage child (and/or living in the household)

Adequate German language skills

Membership of the affected parent in a statutory health insurance

Informed consent for study participation from the patient and/or healthy parent including linkage to questionnaire data and routine data

#### Exclusion criteria

Withdrawal of consent by the affected or healthy parent

Relevant cognitive limitation, advanced dementia

Membership of the affected parent in a private health insurance

Individuals who are in relationships of dependence or employment to the project managers or their representatives

### Primary and secondary outcomes

The intervention effectiveness will be examined using primary and secondary target variables collected at three measurement points, presented in the variables plan (Fig. 2; see the trial Standard Protocol Items: Recommendations for Interventional Trials (SPIRIT) Checklist for details (in Additional file 1)). The primary endpoint is a reduction in anxiety and depressive symptoms in at least one parent, assessed via the HADS response. HADS response is defined as an HADS reduction between T0 and T2 of at least the minimal important difference (MID) of 1.6.

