### Health-economic evaluation

A health economic evaluation in form of a cost-effectiveness analysis (CEA) and a cost-utility analysis (CUA) will be conducted resulting in an incremental cost-effectiveness ratio (ICER) and an incremental cost-utility ratio (ICUR), respectively. The effect parameter employed in the CEA is the primary outcome of the trial. Thus, the ICER will inform about the additional costs of an additional family with at least one parent who experienced a reduction in anxiety and depressive symptoms (assessed by a reduction at the HADS response by 1.6) during the intervention period from T0 to T2. The ICUR will be additional costs per improvement in parents’ quality-adjusted life years (QALYs) in a family, given as an equally weighted sum of QALYs of all parents, during the intervention period from T0 to T2. QALYs are based on the EQ-5D-5L [19] and evaluated by a German tariff [20] to generate utilities. The health economic evaluation will be conducted from the perspective of the SHI and the society.

The effect parameter and the EQ-5D-5L values are taken from the trial. Intervention costs (family-SCOUT salaries and travel costs) derive from the study documentation. Costs regarding physician contacts, hospital stays, medication intake, domestic help, inpatient care, and absent days are received from SHI data during the intervention phase (T0 to T2). In order to account for a societal perspective in the health economic evaluation, additional information is collected via questionnaires at T0 and T2, i.e., absent days as well as out-of-pocket costs induced at physician contacts, therapist contacts, domestic help, and rehabilitation. Indirect costs due to absent days will be evaluated by the human capital approach [21]. Moreover, we will consider family spillover effects as suggested for health economic evaluations with externalities [22, 23] by including health care costs of children which we receive also from SHI data. In particular, spillover effects are introduced based on the approach suggested by Al-Janabi et al. (2016) [24]. Costs and QALYs will not be discounted due to the short intervention period.

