The statistical analysis of the health economic evaluation will follow the intention-to-treat approach. Multiple imputations to account for missing data will be conducted by considering the hierarchical structure of the data (regions and families). In sensitivity analysis, a full-case analysis will be conducted only with those families with complete data. The ICER and ICUR will be calculated based on the respective outcomes and costs of parents within the family (sum of costs induced by all parents of each family) whereas children’s costs are considered as a spillover effect. As health care use might be substantially higher previous to death and the intervention is not intended to have an effect on mortality, in sensitivity analysis, we will rerun the statistical analysis without families that experienced the death of a parent during the intervention phase. The non-parametric bootstrap method will be employed to generate 95% confidence intervals [25, 26]. In order to account for uncertainty, results will be presented on the cost-effectiveness plane and as a cost-effectiveness acceptability curve [27–30].

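### The one-or-two-parent HADS response and the family sums of QALYs and costs depend on how many parents take part, and the primary test does not allow for it

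*Protocol article*

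**What the plan says.** All references are to the protocol article.

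- **Endpoint** (Primary and secondary outcomes): "The primary endpoint is a reduction in anxiety and depressive symptoms in at least one parent, assessed via the HADS response". The threshold follows: "HADS response is defined as an HADS reduction between T0 and T2 of at least the minimal important difference (MID) of 1.6".
- **Who takes part** (Inclusion criteria): "Informed consent for study participation from the patient and/or healthy parent". The description of the intervention names single parents as part of the target group: "Both parents (or a single affected parent) should have the chance to reduce stress levels". Statistical methods nevertheless words the response as if every family had two parents.
- **Design** (Trial design): "quasi-experimental, non-randomized control group design with two study arms". Under Participants, the groups come from different regions and, in Bonn, from different periods.
- **Analysis** (Statistical methods): the primary analysis is Fisher's exact test on family-level response at 9 months, with no strata or covariates. Adjustment comes in secondary regressions, with sociodemographic and disease-related variables and with baseline variables that differ significantly between groups. The number of participating parents is not named.
- **Health economics** (Health-economic evaluation): the QALY measure for a family is "given as an equally weighted sum of QALYs of all parents", and the cost measure is the "sum of costs induced by all parents of each family".

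**The concern.** A response in at least one parent is a maximum over the parents observed. It becomes more likely as more parents are observed, even if no parent is helped. Where every family contributes the same number of parents, or randomisation balances that number, this affects only the level of the rates. Here the number varies by rule and the groups are formed by region and period, so equal composition cannot be presumed. A difference in composition would then appear in the primary result as an intervention effect, or would hide one.

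The family totals of QALYs and costs have the same property, so the cost-utility result could partly reflect how many parents were counted.

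**Working it through.** **The plan's own figures first.** Dropout: 330 × 0.64 = 211 and 230 × 0.64 = 147, as stated. Exact two-sided Fisher power for 28% vs 16% with 330 vs 230 families is 91.7% (stated 90%). For 30% vs 16% with 211 vs 147 it is 86.0% (stated 85%). The power calculation is sound. Its rates are family-level rates given without the mix of one- and two-parent families behind them.

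**Inputs.** From Sample size: 330 and 230 families, 16% control response, 5% level. Assumed, because the article gives no figures: the share of families with two participating parents in each group (a in IG, b in CG), the within-couple correlation of response ρ (0, 0.3, 0.5), and the same response probability p for every parent in both groups, i.e. no intervention effect.

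**One parent versus two.** P(response | one parent) = p. P(response | two parents) = 2p − [p² + ρp(1−p)]. At p = 0.16:

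- ρ = 0: 0.32 − 0.0256 = 0.294
- ρ = 0.3: 0.32 − (0.0256 + 0.3 × 0.1344) = 0.254
- ρ = 0.5: 0.32 − (0.0256 + 0.5 × 0.1344) = 0.227

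With independent parents, the step from one to two parents (16% to 29.4%) is about as large as the contrast the trial is planned to detect.

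**False difference between groups.** Two parents minus one parent equals p(1−p)(1−ρ), so the false difference is (a − b) × p(1−p)(1−ρ). For each row p is set so that the control rate is 16%. Example: a = 80%, b = 60%, ρ = 0 gives p = 0.104, and 0.20 × 0.104 × 0.896 = 0.019. Rejection is the exact two-sided Fisher rejection rate at 330 vs 230.

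| Two-parent share, IG vs CG | False difference in points (ρ = 0 / 0.3 / 0.5) | Rejection (ρ = 0 / 0.3 / 0.5) |
|---|---|---|
| 70% vs 70% | 0 / 0 / 0 | 4.4% / 4.4% / 4.4% |
| 70% vs 60% | +0.9 / +0.7 / +0.6 | 5.2% / 4.9% / 4.7% |
| 80% vs 60% | +1.9 / +1.4 / +1.1 | 7.8% / 6.4% / 5.6% |
| 90% vs 50% | +3.9 / +3.0 / +2.3 | 20% / 14% / 10% |
| 60% vs 80% | −1.7 / −1.3 / −1.0 | 7.7% / 6.4% / 5.6% |

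**QALY sum.** Over 9 months (0.75 years) a second parent adds utility × 0.75. With an imbalance of 10 points the mean family total shifts by utility × 0.75 × 0.10: 0.6 × 0.075 = 0.045 and 0.85 × 0.075 = 0.064 (utilities assumed). This holds if the measure is a sum of QALYs accrued. The article gives no cost figures, so the shift in summed costs and in the ICUR cannot be sized.

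**The case against.** **The secondary analyses may already cover this.** Response in at least one parent is itself a target of the adjusted regressions. Family composition is naturally a sociodemographic variable, and an article need not list every covariate. If the number of parents is among the baseline variables screened, Fisher's test at 330 vs 230 would flag 80% vs 60% in more than 99% of trials and 70% vs 60% in about two thirds. Continuous HADS subscores are also analysed separately for the healthy parent and the parent with cancer, and those outcomes do not grow with the number of parents. This stands, and a reader who infers that nothing in the plan could reveal or remove the bias goes too far. What it does not do is protect the primary test, which remains unadjusted.

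**The bias is small at moderate imbalance.** This also stands. At 10 points the rejection rate is practically nominal. A reader might reach much larger figures by assuming that a third or more of parents improve by chance, but that does not fit the planned 16% per family in the control group.

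**Direction.** A reader might infer that outreach draws partners into the study and so favours the intervention group. The article describes counselling being offered. It does not say that partner participation in the survey rises, and it reports no composition by group. The direction is unknown.

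**Health economics.** The ICUR is worded as cost per improvement in parents' QALYs. If improvement means change from T0, an unchanged second parent adds nothing and the shift calculated above largely disappears. The wording allows either reading. Summed costs depend on the count either way. A family total is a legitimate estimand for a family intervention, so the documents do not support calling it an error.

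**Imputation.** Multiple imputation of HADS might fill in a partner who did not take part, though the article does not say so. It cannot supply a second parent to a single-parent family.

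**Conclusion.** The concern holds as a weakness of the stated primary comparison. Under the article's own rules, response probability rises with the number of participating parents, that number may differ between non-randomised groups, and the primary test ignores it. The false difference is below 1 point for an imbalance of 10 points, 1.1–1.9 points for 20 and 2.3–3.9 points for 40, with rejection of about 5%, 6–8% and 10–20%. It could run in either direction. Against a planned difference of 12 to 14 points this matters only if the imbalance is substantial or the true effect is modest. The QALY total shifts by 0.045–0.064 per 10 points of imbalance if it is read as a sum.

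These sizes rest on assumed two-parent shares, within-couple correlations, equal response probability for every parent, and utilities. The mechanism itself rests only on the article's definitions. The change is worth making because it is nearly free. The material does not show that the trial's result is invalid.

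**What to change.** Settle the following before outcomes are compared between groups:

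1. Stratify the primary comparison by number of participating parents at T0 (one or two), for example with an exact stratified test or a Mantel-Haenszel test. Alternatively, make the regression of family response adjusted for this count the primary analysis.
2. Include the count as a fixed covariate in the secondary family-level models and in the imputation model, whether or not it differs significantly at baseline. The significance screen would miss a 10-point imbalance (70% vs 60%) about one time in three.
3. Report the share of two-parent families by group, and response within each stratum.
4. Report QALYs and costs per participating parent, or adjusted for the number of parents, alongside the family sums. State whether the QALY measure is a total or a change from T0.

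The cost is one more stratification factor, one more set of reported results and wording in the analysis plan. The count is known at T0, so no new data are needed. The change removes only the effect of the count. Other differences between the groups still depend on the adjusted analyses.
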